### Study B (objective 2): Economic evaluation of CFWP intervention(s)

Study B will focus on evaluating the resource implications of the CFWP intervention(s) undertaken in the auto manufacturing and educational services sectors in order to respond to the following question: What are the incremental costs and consequences of the intervention, relative to the status quo (the “do nothing” alternative), from organizational and societal perspectives? As an organizational perspective will only capture costs and consequences accruing to the employer/workplace, this research stresses the importance of a broader and societal level perspective in order to capture the full impact of the intervention to all stakeholders.

The types of economic evaluations to be undertaken are a cost benefit analysis (CBA) and a cost-effectiveness analysis (CEA). The CBA/CEA will analyze the costs and benefits and effects of each intervention(s) chosen for implementation in each of the respective workplaces compared to the status quo (i.e., the “do nothing” alternative). This is a common comparator used in workplace health evaluation when new intervention(s) are being evaluated [41–43]. The resources to be considered in the analysis will include the costs associated with making the intervention(s) available (people time, other resources costs, advertising expenditure, etc.), as well as those gained as a result of fewer sick days taken by caregivers, higher at-work productivity, lower turnover, continued labour force engagement, less use of health services, etc. The process that the CBA/CEA will follow is comprised of: selecting the intervention(s) and comparator time period; identifying stakeholders; measuring all known and quantifiable costs and consequences flowing from the intervention(s); predicting the outcome of cost and benefits/effects over a relevant time period; converting all costs and benefits into a common currency and effect into a common metric; applying a discount rate; calculating the net present value as well as other summary measures, such as the payback period and benefit-to-cost ratio, cost per unit of effect, executing a sensitivity analysis for key values; and reporting findings to the employers and workplace parties.

A before-after study design will be used, in which the before period in the same organization is used as the comparator (i.e., the “do nothing alternative”). CBA/CEA will be undertaken in which all resource implications of the intervention (both costs and consequences) are translated into monometer terms. For CEA, resource implication except the primary effect/outcome will be translation into monetary terms. A stop-and-drop approach will be used in which only those costs and consequences incurred during the measurement time period are considered, as well as a more comprehensive approach to intervention evaluation in which projections are made into the future about the resource implications of the intervention.

This study will attempt to capture as many of the resource implications (i.e. personnel costs, start-up costs, etc.) that follow from the chosen intervention(s), regardless of to whom they fall. Cost and consequences for each of the key stakeholders (i.e. CEs, employers, and society) will also be considered. Given that this study uses a CBA, there will inevitably be some resource implications of importance that are not adequately captured because they are intangible or not measured well in dollars; CEA allows us to keep at least the primary effect/outcome in natural units. This is particularly useful if the effect is better captured by a non-monetary metric, e.g., health. Stakeholders will play a key role in the identification and assessment of the valued resource implications and their relative importance in monetary and non-monetary terms.

In order to control for non-intervention(s) factors that may influence relevant outcomes in the before and after periods, regression modeling analysis (specifically, interrupted time series analysis) for key outcome variables will be undertaken, in which the unit of analysis will be the department per unit of time (often weekly or monthly time units depending on the size of the organization and data availability). Data for explanatory and outcome variables will be drawn from both primary data collection, as well as administrative data sources (i.e. sick days used, vacation days taken, etc.) made available by the employer partner organizations. Regression modeling allows us to control for contextual factors such as changes in the amount of hours worked by the unit, output changes, turnover, and external environment factors. The model will identify both the significance of the intervention(s) impact on the outcome of interest (e.g., sick days used, work/production output), as well as the magnitude of it impact. This information will be used to quantify the consequences of the intervention(s) in terms of changes to the outcome variable, which will then be translated into monetary terms, in the case of CBA, for use in the economic evaluation.

The expected outcomes will include information on the cost and consequences of the CFWP intervention(s) for different stakeholders. The resource implications of interventions are often a critical piece of information for key organizational decision makers, such as employers. Specifically, the impact of an intervention on the financial bottom line can influence whether to invest in, continue with, or expand a particular activity. Knowledge on the societal level economic impacts is also critical since it provides public sector decision makers with an understanding of the spillover effects of CFWPs to other stakeholders, and the merits of providing public support to encourage societally valued interventions.

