Since the 1990s, there has been an increased recognition of the need for financial and job security for caregivers [6–9], as well as relief from the role strain of what has been termed ‘the double day’ or the ‘second shift’. Workplace overload can lead to spill-over effects at home, and home stress due to caregiving can lead to negative effects at work, particularly for women who do not disengage as much after work compared to men [10]. With caregivers in Canada providing an estimated $26 billion of unpaid work, the Canadian health care system relies on informal unpaid care to support an aging population [11]. To address the problem of financial and job security, the Canadian government has implemented a number of programs for caregivers, such as the Compassionate Care Benefit (CCB) and caregiver and other tax credits. However, despite these attempts to provide informal unpaid caregivers with much-needed financial support and respite, policy-makers are coming to the realization that this is not enough. Rather, support needs to come from employers as well [7, 12–15]. For employers, there are several advantages to creating CFWPs. The potential costs of these policies can be offset by increased employee retention and less employee turnover, reduced absenteeism and presenteeism (i.e., engagement in work), and a positive company reputation, which can be beneficial both for business and for employee recruitment [2, 16–20]. In 2007, Canadian businesses lost over $1.3billion in productivity, as a result of informal unpaid caregivers missing full days of work, missing hours of work, or even quitting or losing their jobs [21]. Thus, from a business perspective, employers have much to gain financially from offering CFWPs, while simultaneously decreasing role strain, negative health outcomes and risk of occupational injury for CEs. This not only improves CEs’ job satisfaction but positively impacts CEs’ overall health [22–31]. Considering that informal unpaid caregivers play a significant, dual economic role in Canadian society, it is imperative to seek strategies that minimize or alleviate inequitable caregiver burden and the potential negative health outcomes which can arise for CEs [32].

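### Study B's interrupted time series would adjust for turnover and output changes, which the plan also treats as gains or outcomes of the policy, so the estimate that is valued would not be the total effect

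*Protocol article*

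**What the plan says.** All of this is in the protocol article, Methods, Study B, unless another section is named.

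- **Purpose of the adjustment.** The interrupted time series is run "In order to control for non-intervention(s) factors that may influence relevant outcomes in the before and after periods". The unit of analysis is a department in a week or month.
- **What is adjusted for.** "Regression modeling allows us to control for contextual factors such as changes in the amount of hours worked by the unit, output changes, turnover", with the external environment as a further example.
- **Outcomes of the model.** It is to give the significance and size of the impact on "the outcome of interest (e.g., sick days used, work/production output".
- **Use of the estimate.** "This information will be used to quantify the consequences of the intervention(s) in terms of changes to the outcome variable". For the cost-benefit analysis (CBA) the change is then converted to money.
- **Gains credited to the policy.** Among the resources to be counted are "those gained as a result of fewer sick days taken by caregivers, higher at-work productivity, lower turnover, continued labour force engagement".
- **Scope.** One step of the CBA and cost-effectiveness analysis (CEA) is "measuring all known and quantifiable costs and consequences flowing from the intervention(s").
- **Background section.** "The potential costs of these policies can be offset by increased employee retention and less employee turnover".

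The comparator is the period before launch in the same organisation.

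**The concern.** A covariate belongs in this model if it moves the outcome and the policy does not move the covariate. Season and the outside economy meet that test. Turnover and output do not, on the plan's own account: it expects the policy to reduce the first and raise productivity, and it gives output as a possible outcome. Calling them contextual does not change this.

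The economic question concerns the incremental costs and consequences of the policy against doing nothing, which is a total effect. If a department produces more because fewer people leave, that gain is part of the return to the employer. A model that holds turnover fixed attributes the gain to turnover and takes it out of the policy coefficient. The smaller or otherwise altered coefficient then enters the net present value, the payback period, the benefit-to-cost ratio and the forward projections. Because the comparator is the same organisation's earlier period, no parallel series is described that would reveal the loss.

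**Working it through.** The plan states no effect size or series length for this model, so there is no figure to reproduce. The check compares roles and then works out what the coefficient means.

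**Step 1. Roles given to each variable**

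| Variable | Named as gain or outcome | Named as control |
|---|---|---|
| Turnover | Gain (Study B, Background) | Yes |
| Output | Example outcome (Study B); productivity is a listed gain | Yes, as output changes |
| Hours worked by the unit | Not named; implied only, since the Background lists shorter hours and unpaid leave among common policies | Yes |
| External environment | No | Yes |

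Turnover and output hold both roles. The external environment does not conflict. Hours worked is a borderline case.

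**Step 2. What the adjusted coefficient estimates**

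Let P be the post-launch step, M a variable that P shifts, and Y the outcome.

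- M = aP + other causes
- Y = cP + bM + other causes
- Total effect of P on Y = c + ab
- Coefficient of P with M in the model = c
- Amount removed = ab

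The evaluation needs c + ab. The stated adjustment returns c.

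**Step 3. Illustration with assumed inputs**

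Assumed, not from the documents: 10 departments, 24 time points (12 before launch, 12 after), 400 simulated data sets, and a total effect on output of 1.00. The policy lowers turnover by 0.5 and raises hours by 0.5 standard deviations. A share s of the effect is split equally between these two paths.

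- Strength of each path: b = (s/2)/0.5 = s
- Mediated part: 0.5s + 0.5s = s
- Direct part: 1 − s

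Both models have department effects, a linear trend and a step.

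| s | 1 − s | Step estimate, unadjusted | Step estimate, adjusted |
|---|---|---|---|
| 0% | 1.00 | 0.99 | 0.99 |
| 25% | 0.75 | 1.01 | 0.75 |
| 50% | 0.50 | 0.99 | 0.50 |
| 75% | 0.25 | 1.01 | 0.26 |

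The adjusted estimate matches 1 − s to within 0.01. This confirms the algebra of Step 2 and does not estimate the loss in this study, because s was put in by hand. The simulated turnover and hours also have no outside cause that shifts at launch, so the unadjusted model is right by construction.

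**Step 4. Direction**

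- *Output.* Lower turnover should raise output, so ab has the same sign as the hoped-for effect. Removing it attenuates the estimate.
- *Sick days.* Fewer exits could ease the load on colleagues and reduce sick days, or could keep in post caregivers who use more of them. The sign of ab is open. If something unmeasured, such as workload, drives both turnover and sick days, conditioning on turnover can add a further bias in either direction.

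**Step 5. Route into the economic result**

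Total benefit is a sum over streams of unit value × change. Only the streams whose change comes from the adjusted model are distorted. Valuing turnover separately restores the direct cost of exits avoided, but not the effect of those exits on output or sick days.

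**The case against.** The best defence has three parts.

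**The sentence is illustrative.** It says what regression makes possible and gives examples; it is not a covariate list for each model. This stands in part. A reader might infer that output will be a covariate in the model for output, leaving that effect unidentified. The article does not say so: several outcomes are foreseen, each could have its own covariates, and such detail can be left to a fuller document. What the article does say is that turnover and output changes belong with the non-intervention factors, and that conflicts with its own list of gains however the covariates are later allotted.

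**Leaving these variables out has a cost.** In an uncontrolled before-after design, staffing and production can move for reasons unrelated to the policy, such as demand. This is true and is the real trade-off. It argues for adjusting for the outside causes themselves. Adjusting for turnover or output removes the outside disturbance and the policy's own effect together.

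**Hours worked is a natural exposure term.** More hours give more opportunity for sick days. This stands. A reader might infer that the plan lists hours worked as an effect of the policy; it does not. Since some candidate policies alter hours, scheduled hours would be a safer denominator than actual hours, but hours need not be given up.

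**Conclusion.** The point holds for turnover and output. The plan classes as non-intervention factors two variables that it elsewhere treats as gains or outcomes, and it feeds the resulting coefficient into the economic evaluation. The conclusion assumes that post-launch values would enter the model, which the reference to changes in these variables supports, and that the policy does affect them, which the plan itself expects.

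The size is unknown, because the documents give no mediated share. Two stronger readings should be resisted. A reader might infer that the bias generally runs toward no benefit; that is likely for output, but nothing in the documents settles it for sick days. A reader might also take the percentages in the illustration as the loss in the CBA. They only return the assumed shares, and the CBA adds several streams, not all of which need come from this model.

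**What to change.** In the Study B paragraph on regression modelling:

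1. Remove turnover and output changes from the covariates of the model that feeds the CBA and CEA.
2. Limit time-varying covariates to factors the policy cannot change: season and calendar, shutdowns or term dates, the external environment and, where available, volume set outside the department.
3. Keep hours only as an exposure denominator, preferably scheduled hours where available.
4. Analyse turnover and output as outcomes, each with its own estimate of the policy effect.
5. When adding up the monetary value, avoid counting turnover's effect on output twice. For example, if output is valued from its total effect, value an exit avoided without its lost-production component.
6. Report any model adjusted for turnover, output or actual hours as a labelled sensitivity analysis that does not supply the valued estimate.

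The core change is a matter of wording. Scheduled hours and externally set volume may need further data: the article gives sick days and vacation days as examples of administrative data and does not show that these other items are available. The statistical cost is some residual confounding in the primary estimate if turnover or output also shifts for outside reasons. Comparison with the sensitivity model would show how far the result depends on that choice, though a gap between the two could reflect mediation as well as confounding.

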### Study C (objective 3): Implementation analysis

Framed within a comparative case study design, Study C will undertake an implementation analysis of the CFWP intervention(s) in each participating workplace in order to determine: the degree of support for the intervention(s) (reflected in the workplace culture); how sex and gender are implicated; co-workers’ responses to the chosen intervention(s); and other nuances at play. An implementation analysis is a type of qualitative research study that investigates the determinants involved in the intervention(s)’ deployment and application; the effects of the intervention(s); and the influence of contextual factors on both the application and the effects of the intervention(s). This will translate into knowledge regarding the promotion of equity in the appropriate diffusion and availability of suitable CFWP innovation(s) for both the participating employers, the sectors they represent, and beyond.

Ethnography is appropriate for an implementation analysis as the researcher needs to be fully immersed in the ‘culture’ of the workplace. An ethnographic approach examines a small sample of participants in great depth over an extended period of time. This study will use maximum variation purposive sampling to recruit participants. During the proposed 12 months of fieldwork, data will be generated using participant observation and face-to-face interviews, in order to capture the richness of experiences while gaining insight into the dynamics of the social relations that exist within their historical, geographical, occupational, and cultural contexts. Participant observation will vary by week, but will average two days at each workplace. Here the researcher will observe and interact with the respective employees at break and lunch periods, as well as participate in all regular and special face-to-face meetings regarding the intervention(s), including those scheduled with the employer and research team. The audio-taped, semi-structured in-depth interviews will involve the intervention(s) participants (*n* = 5), as well as the associated human resource personnel (*n* = 3), managers (*n* = 2), administrators (n = 2), as well as co-workers (n = 3). In total, it is estimated that 15 face-to-face, audio-recorded in-depth semi-structured interviews will be conducted in each workplace (total sample will be 30). Each group of employees (intervention(s) participants, HR personnel, managers, administrators, co-workers) will be asked a unique set of questions regarding the implementation of the intervention(s), based on their location within the workplace. Following research ethics approval, these interviews will take place after the initial six month intervention(s) period (that is, half-way through the Study A intervention(s) period of 12 months). This will allow each group of employees to become familiar with the intervention(s) implementation process. The participant observation diaries and in-depth interviews (the latter which will be transcribed verbatim) will be stored and managed in NVivo10. Following a thematic analysis approach, the researchers will examine the textual data thoroughly, through multiple readings. During the readings, recurring themes will be documented in an iterative process.

It is hoped that this study will provide strategies on how to better implement the CFWP intervention(s) in both the workplaces concerned, as well as in other workplace settings. Guided by the thematic analysis approach to data interpretation, and with sex and gender at the centre of the analysis, this research will build on existing research on CFWPs intervention(s) and help in determining employment supports, such as CFWPs, that will assist in mitigating the negative impacts on CEs’ health and physical, psychosocial and mental well-being. Further, the results of the implementation analysis will allow other employers to learn what contributes to the success of CFWP intervention(s). The expected project results will provide the research evidence for extensive knowledge translation (KT) work, in collaboration with the identified KT partners, to the employer/human resources (HR)/occupational health and safety target population.

## Discussion

Given the strong recognition of the importance of the interface of policy, research and community, this project proposes to undertake a number of KT strategies beyond the traditional academic channels. With the assistance of a part-time Research Assistant specifically dedicated to KT, four specific groups of knowledge users will be targeted in order to disseminate the research evidence, so that it can be used to inform further uptake of CFWPs: (1) Canadian employers/HR personnel; (2) occupational health and safety organizations; (3) caregiver-employees; and (4) government and policy/decision makers. KT strategies are discussed in more detail below. KT goals include: integration of sex/gender sensitive CFWPs into workplaces characterized as employing CEs, and educating and advocating for CFWPs. Further, all research outcomes will be made available for dissemination via: (a) the PIs web-page [44]; (b) the web-based technology and network made available by The Canadian Center for Occupational Health and Safety (CCOHS), as well as; (c) hyperlinked on the appropriate web page of the two participating employers, as well as the union which represents employee members in both workplaces.

In addition to a final scientific and lay report, a minimum of five high impact academic conference presentations and three open-access peer-reviewed papers will be realized, targeting reputable occupational health and human resources venues across Canada. End-of-project KT will include a face-to-face KT Community Workshop on Caregiver-Employees, which will also be accessible virtually for those unable to attend in person. This KT Community Workshop will be a half-day meeting where the research results will be presented and strategically discussed, with respect to the desired outcomes specific to the KT and uptake of CFWPs. Invited attendees include: research team members, knowledge user/KT partners, study participants, and the general public. The workshop participants will receive a briefing paper of the results one week before attending the workshop. This will allow them to think through the results while answering pointed questions that will encourage discussion and uptake of the accrued knowledge around CEs and appropriate CFWPs. The outcomes of this workshop will be summarized in the final report to the funder, as well as disseminated via the web-based technology and network made available by all KT partners’ web pages.

